### Randomization Procedure

Randomization of participants to *continuous* or *intermittent* nutrition groups will be performed using the ALEA randomization tool (ALEA Clinical, FormsVision), a dedicated computerized system accessible 24 hours a day and 7 days a week. The computer algorithm allocates every consecutive eligible patient to 1 of the 2 treatment arms in a one-to-one allocation ratio using permuted blocks of 10. Patients will be stratified into 3 age groups: neonates (≤44 weeks PMA), infants (<1 year), and children (≥1 year).

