### Nutritional Support

#### Caloric Intake

During the study, nutritional intake will be provided to both allocation groups according to the current pediatric critical care nutrition guidelines [5,20,21]. In all patients from both study arms, EN will be started as soon as possible (<24 hours), provided that they are hemodynamically stable and without formal contraindications. EN will be administered through a gastric or postpyloric tube and gradually increased using a stepwise protocol (Figure 1), guided by the clinical judgment of the responsible clinician. Caloric goals will be calculated upon admission according to the body weight–based or body weight and length–based Schofield equation for the estimation of REE [22]. In line with the international nutritional guidelines for critically ill children, caloric intake is targeted to reach 1×REE at the end of the first week [5]. After 1 week, caloric target intake increases further to a maximum caloric intake of 1.3×REE for older children and adolescents and up to 2×REE for neonates and infants [20]. The research team will provide nutritional advice based on the standard protocol on a daily basis. The responsible clinician will decide the actual amount of nutrition prescribed based on the protocol, the nutritional intake the day before, and the tolerance of the administered nutrition. If EN cannot be started or increased according to the protocol, the reasons will be recorded in the database.

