### Intervention Group: Intermittent Nutrition

For patients randomized to the *intermittent* nutrition group (intervention group), all nutritional support will be provided during the day and withheld during the overnight feeding interruption period. The overnight feeding interruption period will be designed in an age-dependent manner. The feeding interruption period will be from 2 AM to 10 AM in neonates (≤44 weeks PMA), from 12 AM until 10 AM in infants (<1 year), and from 10 PM to 10 AM in children (≥1 year), as shown in Figure 2. The daily planned nutritional intake will be provided during the condensed feeding period over the day. The starting time of nutritional intake is set to 10 AM to facilitate procedures that require fasting to be performed in the morning. PN (beyond day 7, if necessary) will be provided during the daily age-dependent feeding periods and tapered over 1 hour during the starting and stopping of PN to reduce the risk of swift metabolic shifts (Figure 2) [25,26].

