### Blood Glucose Management

Upon request of the national ethical review board (CCMO) on account of safety concerns, for patients in the intervention group, a glucose intake infusion will be provided during the overnight feeding interruption period (1.0 mg/kg/minute in neonates and 0.5 mg/kg/minute in infants) to reduce the risk of hypoglycemia. In children aged >1 year, no baseline glucose infusion during the overnight feeding interruption period will be provided unless clinically indicated. Glucose level measurements will be performed at least once daily during the feeding period, regularly during fasting intervals and when clinically indicated. Blood glucose management will be performed according to the local protocol. In short, blood glucose levels will be targeted from 4.0 to 7.8 mmol/L in all age groups. In patients with hyperglycemia (glucose >10 mmol/L) in 2 measurements (with 1 hour between measurements), the glucose intake will be first reduced, and if this is not sufficient, a continuous insulin infusion will be started using a stepwise nurse-driven glucose control protocol. If the blood glucose levels are <2.6 mmol/L, a bolus of 1 mL/kg glucose 10% will be provided and the baseline glucose infusion will be increased until the blood glucose level is >4.0 mmol/L. The glucose levels will be measured again within 30 minutes and 1 hour of treatment. In patients randomized in the *intermittent* group, if insulin is provided, this will be stopped 1 hour before the start of the overnight feeding interruption period.

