### Statistical Analysis

#### General Rules

A CONSORT (Consolidated Standards of Reporting Trials) flow diagram will be reported [39]. All analyses will be primarily performed according to an intention-to-treat analysis. To perform additional per-protocol analysis, we anticipated that up to 30% of the patients will not be able to receive artificial nutrition during their admission to the PICU.

Categorical variables will be summarized as counts and frequencies and analyzed using the chi-square test or Fisher exact test. Continuous variables will be summarized using either mean and SD or median and IQR, depending on the distribution of the variables.

All analyses will be performed primarily for the complete group. In secondary analyses, analyses can be stratified according to different age groups (neonates, infants, and children). Adjustment for baseline risk factors, including the diagnostic group, age group, severity of illness, and severity of nutritional risk, will only be used for secondary analyses. Multiple imputation will only be used in secondary analyses to deal with missing data for confounders. For all end points, differences will be considered statistically significant when the 2-sided *P* value is <.05 or when the 1-sided *P* value is <.025 in the case of noninferiority tests, without correcting for multiple testing.

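### Age group stratifies the randomisation but is kept out of the primary ketosis test: a valid, mildly conservative choice that can be improved at no real cost

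*Protocol article*

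**What the plan says.** The Randomization Procedure section of the protocol article fixes the strata: "Patients will be stratified into 3 age groups: neonates (≤44 weeks PMA), infants (<1 year), and children (≥1 year". Within them it uses a "one-to-one allocation ratio using permuted blocks of 10".

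Age group also shapes the trial treatment. The Intervention Group section says "The overnight feeding interruption period will be designed in an age-dependent manner", and the clock times listed there give fasts of 8, 10 and 12 hours. Blood Glucose Management gives the intervention arm an overnight glucose infusion of "1.0 mg/kg/minute in neonates and 0.5 mg/kg/minute in infants", with no routine infusion above one year. The Caloric Intake section lets targets after the first week rise to at most "1.3×REE for older children and adolescents and up to 2×REE for neonates and infants".

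On analysis, the General Rules state "All analyses will be performed primarily for the complete group" and that adjustment for factors including "age group, severity of illness, and severity of nutritional risk, will only be used for secondary analyses". The Primary Outcomes part of the Statistical Analysis then specifies a two-sided t test on each patient's average of the nightly peak ketone values, and a linear mixed model for non-inferiority of caloric intake. Only the analysis plan for secondary outcomes is deferred to a separate publication, so the rule for the primary analyses is fixed here.

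**The concern.** Stratified permuted blocks keep the arms close to balanced on age group. Differences in mean ketones between age groups then contribute almost nothing to the chance variation of the difference between arms. A t test that ignores the strata still counts those differences in its standard error. If age is related to ketone level, the reported standard error is larger than the true one: the confidence interval is too wide, the test rejects less often than its nominal 5% under the null, and some power is given away.

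At stake is efficiency in half of the primary outcome, and consistency between design and analysis. Age was thought important enough to stratify on, yet the primary analysis does not use it. The same rule keeps age group out of the primary caloric-intake model.

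**Working it through.** **Inputs from the article (Sample Size Calculation, General Rules).** Means 0.10 and 0.20 mmol/L, so difference δ = 0.10; SD 0.16; two-sided 5%; power at least 90%; 30% inflation; 140 patients, 70 per arm.

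**Input not in the article.** R², the share of within-arm ketone variance explained by age group. It is assumed, and varied from 0 to 0.3.

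**1. Reproduce the plan's own figure.** n per arm = 2(1.960 + 1.282)² × 0.16² / 0.10² = 53.8, so 54, or 108 in total. 108 × 1.3 = 140.4, which matches the stated 140. Unadjusted power at 70 per arm is 95.9% (95.7% with the t distribution).

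**2. Effect of omitting age, analytically.** The standard error used by the t test is about SE = 0.16 × √(2/70) = 0.02704. With age balanced by design, the true one is SE × √(1 − R²).

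- True type I error: 2[1 − Φ(1.96 / √(1 − R²))]
- Power, unadjusted: Φ((δ − 1.96 × SE) / (SE × √(1 − R²)))
- Power, adjusted: Φ(δ / (SE × √(1 − R²)) − 1.96)

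At R² = 0.2 the true standard error is 0.02704 × √0.8 = 0.02419. Type I error is 2[1 − Φ(2.191)] = 2.8%. Unadjusted power is Φ((0.10 − 0.0530) / 0.02419) = Φ(1.94) = 97.4%. Adjusted power is Φ(4.134 − 1.96) = Φ(2.17) = 98.5%.

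**3. Simulation.** 140 patients, three equally likely strata, permuted blocks of 10 within stratum, total within-arm SD 0.16, age effect the same in both arms; 20,000 runs under the null and 8,000 under each alternative. Each cell gives unadjusted / adjusted.

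| Assumed R² | Type I error | Power, δ = 0.10 | Power, δ = 0.07 |
|---|---|---|---|
| 0 | 4.8% / 4.7% | 95.8% / 95.9% | 72.8% / 72.9% |
| 0.1 | 4.0% / 5.0% | 96.5% / 97.2% | 75.0% / 78.5% |
| 0.2 | 2.9% / 4.9% | 97.0% / 98.1% | 75.5% / 82.0% |
| 0.3 | 2.1% / 5.1% | 97.7% / 99.1% | 76.2% / 86.5% |

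The 0.07 column is a scenario, not a planning value. It equals 0.10 × (1 − 0.30): the General Rules expect up to 30% of patients to be unable to receive artificial nutrition, and the scenario assumes that these patients show no contrast between arms and that the SD is unchanged.

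**4. If age acts only through the intervention.** Take controls flat at 0.10, differences of 0, 0.10 and 0.20 in the three strata, and SD 0.16 within each cell. Averaged over arms, the stratum means then differ by 0, 0.05 and 0.10, with variance 0.05² × 2/3 = 0.00167, about 6% of the total. Simulated power at N = 140 is 94.0% unadjusted and 94.6% adjusted, a gain below one point. With no treatment effect in any stratum and flat controls, both tests reject at about 5%.

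**The case against.** The strongest reply is that nothing the plan promises is missed. The t test is unbiased here, its type I error is not inflated, and at the planned difference it exceeds the stated 90% power without adjustment. Age-adjusted and age-stratified analyses are already foreseen as secondary, and an unadjusted primary analysis is transparent and errs on the safe side. All of this stands, and it limits the size of the point.

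A second reply concerns mechanism. Fast length and overnight glucose differ by age only in the intervention arm. That makes the treatment effect vary with age; it does not by itself create an age effect shared by both arms. Step 4 shows that heterogeneity alone yields little. An R² of 0.2 or 0.3 would need ketones to differ clearly by age in continuously fed children too, and the article gives no figure for that. This also stands. A reader might infer that the true type I error is below 5% as a matter of fact; it is so only if such a shared age effect exists.

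A third temptation is to use 49 evaluable patients per arm (70 × 0.7). At R² = 0.1 that gives 88.4% unadjusted against 90.3% adjusted, which would suggest that the power target is missed. The article does not support this reading for the primary analysis: it ties the 30% to an additional per-protocol analysis, the primary analysis is by intention to treat, and ketones are to be measured daily in all patients.

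What the replies do not remove is the asymmetry. If age is irrelevant, adjustment costs two degrees of freedom and no visible power; if age matters, it helps.

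**Conclusion.** The point holds as a free improvement of modest size. The primary ketosis test ignores the randomisation strata; if age explains any ketone variance, it is valid but conservative and less efficient than an age-adjusted analysis. Under the article's own assumptions the gain is nil at R² = 0 and about 1 to 1.5 points at R² = 0.2 to 0.3. It reaches about 3 to 10 points (R² 0.1 to 0.3) only under the assumed diluted difference of 0.07. In that scenario most of the shortfall from 90% comes from the dilution and would remain in part after adjustment.

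A reader might also infer a power loss in the caloric-intake half of the primary outcome. The documents do not allow that to be sized: no SD for intake is given, intake is already expressed relative to each child's estimated energy expenditure, and the differing upper targets apply only after the first week. Including age group there is justified by consistency with the design, not by a computed loss.

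**What to change.** Specify the primary ketosis analysis as a linear model on patient means with arm and the three-level randomisation age group as terms. Include the same age group in the primary mixed model for caloric intake. Reword the General Rules so that the restriction to secondary analyses covers the other baseline factors but not the stratification factor. Keep the unadjusted t test as a sensitivity analysis, and report estimates by age group descriptively.

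The cost is a sentence or two in the plan and two degrees of freedom. No new data are needed, because age group is recorded at randomisation. With 132 of 140 patients already included by May 2022, the change should be dated and fixed before anyone examines outcome data by arm.

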#### Primary Outcomes

To assess a significant difference in ketosis between the 2 arms, a 2-tailed *t* test will be performed on the patient means of the highest ketone levels in each fasting period (or similar time point in the control group). A linear mixed model will be used to assess the noninferiority of caloric intake (repeatedly measured over time) in the intervention group, with a noninferiority margin of 33%.

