**Figure 2 figure2:**
[figure not shown]
Randomization and age group–specific feeding schedules and measurements. Glucose and ketone level measurements are indicated with black arrows; during the fasting interval these measurements are performed at set time points (black arrows without asterisk); during feeding these measurements are performed regularly, but not at specific time points (black arrows with asterisk). Blood samples for metabolism analyses are at set time points in both fasted and fed state and are indicated with red arrows. *Parenteral nutrition is only supplied in the second week of pediatric intensive care unit (PICU) admission, when enteral nutrition is insufficient. For details, see text. EN: enteral nutrition; PN: parenteral nutrition.

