### Study Blood Samples

For all patients, daily plasma glucose levels will be measured and analyzed at the bedside using a blood gas analyzer (ABL90 FLEX PLUS, Radiometer) or point of care meter (Accu-Chek Inform II, Roche Diabetes Care), and daily ketone levels (3-β-hydroxybutyrate) will be measured using the StatStrip Glucose/Ketone meter (Nova Biomedical). In the *intermittent* feeding group, glucose and ketone levels will be measured more frequently during the feeding interruption period (Figure 2).

Additional blood samples for other analyses of metabolism (eg, glucagon, insulin, and free fatty acids) and circadian rhythm (eg, gene expression and cortisol and melatonin) will be taken upon ICU admission and on days 3, 7, and 14 (Figure 2). The blood samples for metabolism will be collected using serum-separating tubes in both fasted (before 10 AM) and fed states (before 10 PM, 12 AM, or 2 AM, depending on the age group) for the intervention group or at similar time points for the continuous group. The blood samples for circadian rhythm will be collected in EDTA tubes every 4 hours during a 24-hour period (a total of 7 samples per 24 hours). The blood samples for gene expression will be collected in *PAXgene* RNA tubes (PreAnalytiX) once daily on the selected days at 10 AM. These additional blood samples will be taken from lines placed for clinical purposes or in combination with draws requested for clinical purposes. Owing to ethical considerations, the number of blood samples will be calculated using the body weight of the individual patient to ensure a maximum of 5% of blood volume for the entire study.

After collection, the blood samples will be immediately stored in a refrigerator. Within 24 hours after collection, the blood samples from serum-separating tubes and EDTA tubes will be centrifuged at 20 °C, and serum or plasma will then be separated and stored at −80 °C for future measurements. The *PAXgene* tubes will not be centrifuged and will be first stored at −20 °C for 1 day before storage at −80 °C to prevent breakage of the tubes. In addition, plasma phosphate, magnesium, and potassium levels will be determined in residuals of clinical plasma samples by the clinical chemical laboratory on days 0 to 4, 7 to 10, and 14.

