### Sample Size Calculation

To provide a careful estimate of the number of patients required to answer whether the intervention is feasible, we based the sample size on a (1) a fasting response with ketogenesis and (2) sufficient nutritional intake.

We calculated the sample size to detect a fasting response with ketogenesis. In adults who are critically ill (n=70), 12 hours of fasting increased ketones compared with full feeding periods (ketones +0.47, SD 0.07 mmol/L; *P*<.001) [40]. In a study of healthy children, ketones increased from 0.08 mmol/L in the fed state to 0.34 mmol/L (90% CI 0.02-1.78 mmol/L) after 15 hours of fasting [41]. Using these data, we assumed baseline ketones of 0.10 mmol/L (fed state) and 0.20 mmol/L in the fasted state, with an SD of 0.16 mmol/L. To perform additional per-protocol analysis, we increased the sample size by 30%. Ultimately, the sample size of 140 should be able to detect, with at least 90% power (2-tailed power) and 95% certainty, the assumed increase in mean ketone levels of 0.10 mmol/L. Regarding nutritional intake, we considered a reduction in cumulative (caloric) intake, corrected for PICU length of stay, of >33% in the intervention group as clinically relevant based on the currently available literature [2]. The sample size (N=140, 70 per arm) is expected to be able to detect, with at least 80% power (1-tailed power) and 80% certainty, a reduction of 33% in cumulative caloric intake.

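### As worded, the primary ketone endpoint sets the highest of several overnight readings in the intermittent arm against a similar time point in controls, which favours the intervention unless controls have equal readings and their maximum is used

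*Protocol article*

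**What the plan says.** The Primary Outcomes part of the Statistical Analysis section fixes the summary measure, the comparator and the test: a two-tailed t test on "patient means of the highest ketone levels in each fasting period (or similar time point in the control group"). The intermittent arm contributes a maximum over a period. The control arm contributes a value at a time point, in the singular.

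Study Blood Samples sets the sampling. For all patients, "daily ketone levels (3-β-hydroxybutyrate) will be measured using the StatStrip Glucose/Ketone meter". It then adds, for one arm only: "In the *intermittent* feeding group, glucose and ketone levels will be measured more frequently during the feeding interruption period".

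The Figure 2 legend says of the readings that "during the fasting interval these measurements are performed at set time points", whereas "during feeding these measurements are performed regularly, but not at specific time points". Controls are fed around the clock, with planned interruptions of at most 2 hours.

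The Sample Size Calculation rests on mean levels, not maxima: "we assumed baseline ketones of 0.10 mmol/L (fed state) and 0.20 mmol/L in the fasted state, with an SD of 0.16 mmol/L".

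**The concern.** If ketone readings vary at all within a night, the highest of several is larger on average than a single one. An arm that is sampled more often and summarised by its maximum will therefore show higher values than an arm with fewer readings, even when the underlying ketone levels are identical. The excess is a shift in the mean of every nightly value, so averaging a patient's nights reduces the noise but leaves the shift in place.

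Ketosis is one of the two components of the primary outcome and is the evidence that a fasting response occurred. The planned effect is only 0.10 mmol/L, so a shift of a few hundredths is not negligible. Part or all of a positive result could reflect how often patients were sampled.

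**Working it through.** **The plan's own figure.** Inputs from the Sample Size Calculation: difference 0.20 − 0.10 = 0.10 mmol/L, SD 0.16, 90% power, two-sided 5%. Per arm, n = 2 × (1.960 + 1.282)² × 0.16² / 0.10² = 53.8, so 54. With the 30% increase, 2 × 54 × 1.30 = 140.4, which agrees with 140. The sample size arithmetic is not in dispute. It describes a difference in means and makes no allowance for a maximum in one arm.

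**Expected bias with no true effect.** For k independent normal readings per night with within-night SD s, the highest exceeds a single reading on average by c(k) × s, with c = 0.56, 0.85 and 1.03 for k = 2, 3 and 4.

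**False-positive rate.** Assumptions not in the documents: one control reading per night, k = 2 to 4, 5 nights, between-patient SD 0.15, and independent normal readings. The 70 per arm is the plan's. The between-patient SD of 0.15 gives patient means an SD of about 0.15 to 0.16, close to the plan's 0.16. Simulated rejection in favour of the intervention (nominal 2.5%):

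| Within-night SD (mmol/L) | Bias, k = 2 / 3 / 4 (mmol/L) | Rejection, k = 2 / 3 / 4 |
|---|---|---|
| 0.03 | 0.017 / 0.025 / 0.031 | about 10 / 16 / 23% |
| 0.05 | 0.028 / 0.043 / 0.052 | about 18 / 38 / 53% |
| 0.10 | 0.056 / 0.084 / 0.103 | about 56 / 89 / 97% |

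Repeat simulations differ by a point or two.

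One cell by hand, s = 0.05 and k = 3: the variance of a patient mean is about 0.15² + 0.05²/5 = 0.0230 in controls. It is slightly less in the intermittent arm, because a maximum varies less than a single reading. The standard error of the difference is about √(2 × 0.0230/70) = 0.0256. The bias of 0.0425 is 0.0425/0.0256 = 1.66 standard errors, and P(Z > 1.96 − 1.66) = P(Z > 0.30) = 0.38.

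**Averaging over nights.** In a second simulation, total SD was held at 0.16 with 25% of the variance within patient and k = 3 against one reading. The bias was 0.067 to 0.068 mmol/L for 1, 3 and 7 nights alike.

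**Equal counts.** In the same set-up with 3 nights, highest of 3 against highest of 3 gave a mean difference of 0.000 and a two-sided error of 5.1%. One against one gave 0.000 and 4.7%. The problem comes from the unequal count.

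**Less favourable assumptions for the concern.**
- If readings within a night are correlated at 0.7 and the total within-night SD is 0.05, the effective SD is 0.05 × √0.3 = 0.027. Rejection in favour of the intervention falls to about 9, 14 and 20% for k = 2, 3 and 4.
- With total SD 0.16, 10-50% of the variance within patient and 3 nights, lognormal readings gave two-sided error of 10-49% at k = 2 and 30-94% at k = 4. Normal readings gave 19-85% and 52-100%.

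**The case against.** The strongest objection is that the control schedule is drawn in Figure 2, which is not available here. The number of overnight readings in either arm is unknown, and neither a daily nor a regular reading fixes the control count at one. The endpoint wording could also be taken to mean the highest value over the matching period in controls, and the phrase about a similar time point implies some clock matching. If controls had the same number of overnight readings and their maximum were used, the bias would disappear. This stands, and it is why the point is conditional. The text still leans the other way: the extra overnight readings are given to one arm only, and the control comparator is a single time point. The similar time points for controls mentioned under Study Blood Samples belong to the metabolism samples on admission and days 3, 7 and 14, not to the daily meter ketones.

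The size is also open to challenge. Independent readings are the unfavourable case, and normal readings with mean 0.10 and SD 0.15 would imply many impossible negative values. This stands too. Correlation and skewness shrink the inflation, although it stayed above the nominal level in every case examined. A bias as large as the whole planned effect needs four readings and a within-night SD equal to the assumed fed-state mean.

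The planned mixed models for the course of ketones do not use the nightly maximum. They are secondary, so they do not repair the primary test.

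**Conclusion.** On the natural reading of the text, the primary ketone comparison is biased in favour of the intervention and its two-sided 5% error rate does not hold. The direction needs only two conditions: readings vary within a night, and the intermittent maximum is taken over more readings than the control value. The size rests on assumed readings per night, within-night SD and independence. Across the assumed range it runs from about 0.02 to 0.10 mmol/L, with 10-97% false positives in favour of the intervention, and somewhat less when readings are correlated or skewed.

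A reader might infer that the trial will show significant ketosis even if fasting does nothing, or that any positive result is an artefact. The documents support neither. Significance is not certain under the smaller assumptions, the number of control readings is not stated in the available text, and a real ketogenic effect may well be present. What is established is that the endpoint as worded cannot separate such an effect from sampling frequency unless the counts are equal.

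**What to change.** Before unblinding, base the primary test on the same number of clock-matched readings per night in both arms, averaged per patient. There are two ways to do this:

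- **One reading per night:** the last before 10 AM in the intermittent arm, against the control reading nearest that time within a prespecified window.
- **Equal-count maximum:** the highest over equal numbers of readings, matched on clock time, in both arms.

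State which is primary, and keep the unequal-count nightly maximum as descriptive only. If Figure 2 already gives controls equal overnight readings, stating that their maximum over the same times is used would be enough.

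Cost: a change of endpoint wording and no new samples. With 132 of 140 patients included by May 2022, the fix must work with the readings already taken. Under the single-reading option, some signal is lost if the ketone peak comes before the end of the fast. Control readings may have had no fixed times, so an unknown and possibly large number of control nights could have no reading in the window. Treat these nights as missing, report their number, and check sensitivity to a wider window.

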### Outcome Measures

#### Primary End Points

The primary outcome of this study will be the feasibility of a daily feeding and fasting cycle (*intermittent feeding* strategy) compared with a continuous 24 hours per day feeding strategy in critically ill children. The primary outcome is defined as the difference in ketosis (3-β-hydroxybutyrate levels) between the groups under the condition of noninferiority regarding caloric intake. The amount of nutritional intake is defined as the daily caloric intake as a percentage of the estimated REE based on the body weight–based or body weight and length–based Schofield equation.

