**Nutritional intake**
The proportion of patients receiving at least a caloric intake of 67% of predicted resting energy expenditure (pREE) before or at the end of the first week and the proportion of patients receiving at least a caloric intake of 100% of pREE before or at the end of the first weekThe proportion of days caloric targets are reached divided by the total days in the study per patientMedian caloric intake as a percentage of pREEThe proportion of patients requiring supplemental parental nutrition beyond day 7The time to oral intake

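### The 33% noninferiority margin for caloric intake, which gates the primary outcome, is not fixed on one scale: the sample size reads as a relative reduction, the analysis model as percentage points of REE

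*Protocol article*

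**What the plan says.** All references are to the protocol article.

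- **Primary End Points** makes the primary outcome the "difference in ketosis (3-β-hydroxybutyrate levels) between the groups under the condition of noninferiority regarding caloric intake". It measures intake as "daily caloric intake as a percentage of the estimated REE", with REE estimated by the Schofield equation.
- **Statistical Analysis, Primary Outcomes** uses a linear mixed model to assess "noninferiority of caloric intake (repeatedly measured over time) in the intervention group, with a noninferiority margin of 33" per cent. It does not say whether this is per cent of control intake or percentage points of REE.
- **Sample Size Calculation** regards "a reduction in cumulative (caloric) intake, corrected for PICU length of stay, of >33% in the intervention group as clinically relevant", citing literature, and states that 70 patients per arm suffice for that reduction.
- **Caloric Intake** says that "caloric intake is targeted to reach 1×REE at the end of the first week". After week 1 the target may rise to at most 1.3×REE in older children and adolescents, and up to 2×REE in neonates and infants. **PN Support** gives no supplemental parenteral nutrition in week 1.
- **Textbox 2, Nutritional intake** lists as a secondary outcome the proportion of patients with "at least a caloric intake of 67% of predicted resting energy expenditure (pREE") by the end of week 1.
- **General Rules** tests noninferiority at one-sided P<.025.

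**The concern.** A percentage reduction in an arm's cumulative calories is ordinarily read as a share of what the other arm received. A limit placed on the treatment coefficient of a linear model, when the outcome is already in per cent of REE, is ordinarily read as a number of percentage points of REE. The article uses the same 33% in both places and converts neither into the other.

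This is the threshold on which the feasibility conclusion turns. If the scale is still open when the data are in, the same estimates could pass under one reading and fail under the other. On the point reading, the loss tolerated relative to control would also depend on how much the control arm happened to receive, and hence on the age mix and the balance of week 1 and week 2 days.

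**Working it through.** **1. The plan's own figures.** The total of 140 comes from the ketone comparison. With a difference of 0.10 mmol/L, SD 0.16, two-sided 5% and 90% power, n per arm = 2 × (1.960 + 1.282)² × (0.16/0.10)² = 53.8, so 54. Then 54 × 2 × 1.3 = 140.4, which reproduces 140. The power statement for caloric intake cannot be reproduced on either scale, because no control mean and no SD of intake are given. It therefore does not reveal which scale was meant.

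**2. When the two readings agree.** Let C be the mean control intake in % of REE. A 33-point margin allows a relative loss of 33/C. A 33% relative margin equals 0.33 × C points. They coincide only at C = 100. The values of C below are assumptions.

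| Control mean C (% of REE) | Relative loss allowed by 33 points | 33% relative, in points |
|---|---|---|
| 50 | 66% | 16.5 |
| 60 | 55% | 19.8 |
| 80 | 41% | 26.4 |
| 100 | 33% | 33.0 |
| 130 | 25% | 42.9 |

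**3. Where C is likely to lie.** In week 1 the target reaches 100% of REE only at the end, enteral feeding is built up stepwise, and parenteral nutrition does not fill the gap. An average below 100% is therefore plausible. Every patient contributes early days, and only longer stayers contribute week 2. In week 2, targets of 1.3 to 2×REE make averages above 100% possible. The daily targets are in a figure that is not reproduced in the text available here, and no expected average is stated.

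**4. Consequence of using points when relative was meant.** Suppose the true relative loss is exactly 33%, so that a relative test should declare noninferiority 2.5% of the time. With 70 per arm, one-sided 0.025 and an assumed SD of patient-level mean intake:

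SE = SD × √(2/70) = 0.169 × SD

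P(noninferior) = Φ[(33 − 0.33C)/SE − 1.96]

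Worked case, C = 60 and SD = 30: SE = 5.07; (33 − 19.8)/5.07 = 2.60; 2.60 − 1.96 = 0.64; Φ = 74%.

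| C | SD 25 | SD 30 | SD 40 |
|---|---|---|---|
| 50 | 97% | 90% | 68% |
| 60 | 88% | 74% | 50% |
| 80 | 35% | 25–26% | 16% |
| 100 | 2.5% | 2.5% | 2.5% |
| 130 | <0.1% | <0.1% | <0.1% |

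This treats the mixed model as a comparison of patient-level means, which is enough to show the direction and rough size.

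**The case against.** The strongest reply is that there is no contradiction, only a missing unit. The Primary Outcomes section never says percentage points, and the Sample Size section never says relative. A linear mixed model can test a relative margin through a suitable contrast, so both sections may mean the same thing. It can be added that a full analysis plan would normally settle the contrast. Part of this stands: the point reading is an inference from the endpoint and the model, not a statement in the text. It does not dispose of the matter. The model and margin for the primary outcome are set out here, and the article defers only the secondary outcomes to a separate plan. The two sections as written lead a reader to different tests.

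Second, the 67% of REE threshold in Textbox 2 equals 100 minus 33 points, so the 33% may have been anchored to REE all along. That is fair, and it leaves real doubt about which scale was intended. It argues for stating the scale and does not resolve it.

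Third, a reader might infer two stronger things.

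- One is that the plan accepts losing half or more of control calories. That needs both the point reading and a control mean of 66% of REE or less (33/0.5 = 66). The documents establish neither, and above 100% of REE the point margin is the stricter one.
- The other is that the two sections analyse different endpoints. Cumulative intake corrected for length of stay is in substance close to average daily intake. The two may differ in how patients and days are weighted and in scaling to REE, but this is not a clear conflict.

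**Conclusion.** The point holds in this form: the scale of the margin that gates the primary outcome is not fixed, and its natural reading differs between the sample size section and the analysis section. The readings agree only at a control mean of 100% of REE.

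The practical effect depends on an average that the article does not give. At assumed control means of 80%, 60% and 50%, a 33-point margin would pass a true 33% relative loss with probability about 16–35%, 50–88% and 68–97%, instead of 2.5%. At 130% the error runs the other way. These figures rest on assumed means, on assumed patient-level SDs of 25 to 40 points, on 70 analysable patients per arm and on a normal approximation. The documents do not show that the trial will accept such losses. They show that the plan does not exclude it, and that the choice between readings could be made after the data are seen. It should be settled before the intake data are compared by arm.

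**What to change.** State one estimand and one scale in both Primary Outcomes and Sample Size Calculation.

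To match the sample size justification: declare noninferiority if the lower one-sided 97.5% confidence bound of (intermittent mean − 0.67 × continuous mean) is above zero, with both means in % of REE taken from the mixed model over the intervention period. When the continuous mean is positive, this asks whether the ratio of means exceeds 0.67.

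If percentage points of REE were intended, say so, and justify 33 points against the control mean expected over the intervention period.

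Under either choice, give the assumed control mean and SD of intake so that the power statement can be checked.

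**Cost.** One sentence in each section and one model contrast; no new data. When control intake averages below 100% of REE, the ratio test is stricter than the point reading and has less power. Its SE, for equal SDs, is SD × √((1 + 0.67²)/70) = 0.144 × SD. With no true difference and an SD of 40 points (SE 5.75), power is Φ(0.33C/5.75 − 1.96): about 82% at C = 50, 93% at C = 60 and over 99% at C = 80. The 33-point margin gives Φ(33/6.76 − 1.96), also over 99%, at every C. On these assumptions the loss is affordable.
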